### Trial interventions

There are five pairs of interventions being tested in the trial; however, each participating hospital only takes part in three of these five possible comparisons. The non-allocated comparisons and all other aspects of the caesarean section are performed at the discretion of the surgeon.

1. Blunt versus sharp abdominal entry

2. Exteriorisation of the uterus for repair versus intra-abdominal repair

3. Single versus double layer closure of the uterus

4. Closure versus non-closure of the peritoneum (pelvic and parietal)

5. Chromic catgut versus Polyglactin-910 for uterine repair

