### Primary comparative analyses

The primary analyses will be performed on each of the five pairs of surgical techniques. Outcomes will be summarised by intervention group using appropriate summary statistics (counts and percentages, means and standard deviations, or medians and inter-quartile ranges). Comparisons will be made using relative risks (RR) for dichotomous/categorical outcomes, mean differences for normally distributed continuous outcomes, or median differences for skewed continuous variables (unless the data can be transformed to normality). Analysis of time to event outcomes will employ survival analysis techniques [26].

Multiplicity of statistical testing will be addressed in the detailed statistical analysis plan.

With regard to the analysis of child outcomes, multiple births will be treated as independent events in the primary analysis, in order that relative risks may be presented.

Adjusted analyses will be performed on all comparisons to investigate the impact of minimsation factors ‘In-labour or not in-labour caesarean section’ and ‘number of previous caesarean sections (none or one)’. These will be agreed by the investigators and the Study Steering Committee and pre-specified in the SAP.

Subgroup analyses will be similarly agreed and pre-specified in the statistical analysis plan and results will be presented on forest plots, by intervention pair, wherever appropriate.

The robustness of the results will be examined in sensitivity analyses by using multiple imputation techniques to impute missing 3 year follow-up data, and also restricting analyses to a pre-specified follow-up window. Sensitivity of the effect estimates to adjustments for potential clustering of multiple births will also be examined.

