**For women who have a subsequent pregnancy (number estimated to be ~5,900)**				
Uterine rupture or dehiscence	4%	5.9%	1.9%	92%
Preterm birth	10%	7.5%	2.5%	93%

The power calculations in Table 2 assume equal numbers in each comparison and a 2-5% level of statistical significance.

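### The primary relative risk leaves out the two minimisation factors, so it is conservative and less precise than it need be for common outcomes they predict, chiefly mode of delivery

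*Protocol article*

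**What the plan says.** The relevant text is in the protocol article under Primary comparative analyses. The effect measure is given without any covariate: "Comparisons will be made using relative risks (RR) for dichotomous/categorical outcomes". For child outcomes, the same section says "multiple births will be treated as independent events in the primary analysis, in order that relative risks may be presented", which also points to a simple relative risk.

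The balancing factors come in afterwards: "Adjusted analyses will be performed on all comparisons to investigate the impact of minimsation factors", namely "In-labour or not in-labour caesarean section’ and ‘number of previous caesarean sections (none or one". On these adjusted analyses it adds: "These will be agreed by the investigators and the Study Steering Committee and pre-specified in the SAP".

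The word 'unadjusted' does not appear. Even so, the natural reading is that the crude relative risk leads and the adjusted one is an extra analysis, run to see what the factors do.

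**The concern.** Minimisation makes the arms alike on its factors. The part of the outcome variance that lies between factor levels therefore contributes little to the difference between arms, but a crude variance formula still counts it. Where the factors predict outcome, the crude standard error is too large, the interval too wide and the test conservative. An adjusted analysis corrects this and also estimates the effect more precisely.

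The outcome most exposed is mode of delivery in the next pregnancy. It is common and plausibly depends strongly on previous caesarean. Table 1 marks it as a main comparison for single versus double layer closure and for catgut versus Polyglactin-910. At stake is some precision and power in the analysis that will be reported first.

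**Working it through.** **1. The plan's own power figures.** Inputs are the Table 2 rates, about 7,400 women (3,700 per arm) or about 5,900 (2,950 per arm), and a two-sided 5% level. The level is printed unclearly ("The power calculations in Table 2 assume equal numbers in each comparison and a 2-5% level of statistical significance"), but of the levels tried only two-sided 5% reproduces the table. With the pooled-variance normal approximation and no covariates:

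| Outcome | Rates | Stated | Recomputed |
|---|---|---|---|
| Involuntary infertility | 3% vs 4.5% | 92% | 92.5% |
| Subsequent pregnancy | 48% vs 44% | 93% | 93.2% |
| Dyspareunia | 19% vs 16% | 92% | 92.5% |
| Rupture or dehiscence | 4% vs 5.9% | 92% | 92.0% |
| Preterm birth | 10% vs 7.5% | 93% | 92.5% |

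Table 2 is thus the power of an unadjusted test, and it holds for one.

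**2. A strongly predicted common outcome, with full balance.** These inputs are assumed, not documented: a share w = 0.3 has a previous caesarean, and the risk of caesarean at the next birth is 0.5 without one and 0.9 with one.

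- Overall risk: 0.7 × 0.5 + 0.3 × 0.9 = 0.62.
- Total variance: 0.62 × 0.38 = 0.2356.
- Within-level variance: 0.7 × 0.25 + 0.3 × 0.09 = 0.2020.
- Between-level variance: 0.2356 − 0.2020 = 0.0336.
- Crude over adjusted interval width: √(0.2356/0.2020) = 1.080, so about 8% wider.
- If every randomised woman were analysed, the effective critical value would be 1.96 × 1.080 = 2.117 and the type I error 3.4%. Where an adjusted test has 80% power, the crude test has Φ(2.802 − 2.117) = 75.3%.

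**3. Allowing for follow-up and pregnancy.** Mode of delivery is analysed mainly in women who are followed up and pregnant again. Under Sample size and power this is 0.80 × 0.80 = 0.64 of those randomised. If a fraction q is retained independently of arm, only about q of the between-level variance is removed by design, so the true crude variance is 0.2020 + (1 − q) × 0.0336.

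| q | True variance | Crude SE too large by | Type I error |
|---|---|---|---|
| 1 | 0.2020 | 8.0% | 3.4% |
| 0.64 | 0.2141 | 4.9% | 4.0% |
| 0.37 | 0.2232 | 2.7% | 4.4% |

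The value 0.37 is 0.80 follow-up × 0.46, the midpoint of the 44% and 48% subsequent-pregnancy rates in Table 2.

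The power gap remains. At q = 0.64, in units of the crude standard error, the mean is 2.802 × √(0.2020/0.2356) = 2.594 and the true SD is √(0.2141/0.2356) = 0.953. Power is then Φ((2.594 − 1.96)/0.953) = 74.7%, where the adjusted test has 80%.

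**4. Range over other assumed inputs.**

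- w = 0.3, risks 0.6 and 0.9: crude interval 4.7% wider than the adjusted one. Type I error is 4.0% with full balance and 4.4% at q = 0.64.
- w = 0.4, risks 0.4 and 0.9: interval 15.5% wider. Type I error is 2.4% with full balance and 3.2% at q = 0.64.
- Simulation with full balance, vaginal birth 30% versus 5% by previous caesarean: a Mantel-Haenszel relative risk gives intervals about 3% to 4.5% narrower and 1 to 4 points more power.
- The same at 50% versus 2%: intervals 8% to 13% narrower. Power at a relative risk of 0.90 rises from 88% to 92%, or from 77% to 85%, depending on the share with a previous caesarean.

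**5. Rare outcomes.** Assume 50% in labour, 25% with a previous caesarean, and each factor multiplying risk by 3. Power, crude to adjusted, goes from 92.7% to 93.1% for infertility and from 92.4% to 92.9% for rupture or dehiscence. With w = 0.3 and risks of 2% and 4%, the crude interval is 0.2% wider and type I error is 5.0%.

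**The case against.** The strongest reply is that adjusted results are already promised for every comparison, under the heading of the primary analyses, with details to be fixed in an SAP that is not shown. The precise estimate will therefore exist, and what remains is which of the two leads. This stands as a limit on severity. It does not remove the point, because the article already gives the factors a role, as a side analysis of impact, and an SAP that follows its wording would keep the crude relative risk in front.

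A second reply is that most main comparisons in Table 1 concern uncommon events, for which adjustment changes almost nothing. This also stands. The material case is essentially mode of delivery, for two pairs.

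A reader might infer more than the documents support:

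- *That false positives are inflated or estimates biased.* The error runs the other way, and there is no bias.
- *That the Table 2 power is overstated.* It reproduces for an unadjusted test. The loss is only relative to an adjusted analysis.
- *That the authors can choose between crude and adjusted results after seeing the data.* The commitment to pre-specify the adjusted analyses in the SAP undercuts this.
- *That centre or country is also a neglected balancing factor.* Only labour status and previous caesareans are named as minimisation factors. That each hospital runs three of the five comparisons does not make hospital one of them.

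**Conclusion.** The concern holds as a minor point of efficiency and calibration. For common outcomes that the two factors strongly predict, a crude primary relative risk is less precise than an adjusted one, and its test is conservative. In the worked example the crude interval is about 8% wider than the adjusted one. With about 64% of randomised women analysed, crude standard errors are about 5% too large, type I error is about 4.0%, and power is about 75% against 80%. For infertility and uterine rupture the gain is under 1 power point.

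The direction is firm, but the size is not. It rests on assumed factor prevalence and risks, on close balance at randomisation, and on retention that does not depend on arm. The article gives no figures for the first and does not describe the minimisation procedure. The reading of the primary relative risk as crude is the natural one, though it is not stated in so many words.

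**What to change.** State in the SAP that the primary estimate is the relative risk adjusted for the two named minimisation factors, by Mantel-Haenszel stratification or by log-link Poisson regression with robust standard errors. Both keep the relative-risk scale, so the wish to present relative risks is no obstacle. Report the crude relative risk as supportive, and name it in advance as the fallback where events are too sparse for adjustment, with the sparseness rule written down.

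The cost is a few lines of SAP text. Both factors were used at allocation, and adjusted analyses are already planned for all comparisons. No sample size or data collection changes, and Table 2 can stand.

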### Sample size and power

The original sample size for the main trial was calculated assuming a 15% primary outcome event rate in the control group (80% power, 5% two-sided significance level, ability to detect a relative risk of 0.85, 15% loss to follow-up) which resulted in a total sample size required of ~ 15,000 women (~ 9,000 in each intervention pair). The actual overall event rate observed during the conduct of the trial was found to be around 9%. The sample size was increased to 15,492 (9,296 per intervention pair) to account for the reduction in the event rate and agreed by the TSC.

Assuming an overall response rate of at least 80% for the follow-up [27,28], this will provide us with information from ~12,400 women (or ~7,400 for each intervention pair). If we assume approximately 80% of these women will have had a subsequent pregnancy this will result in ~5,900 women in each intervention pair. This number will be sufficient to detect modest but clinically important differences between any principal comparison for this population.

The statistical power available, based on a fixed sample size, for a range of event rates on a selection of outcomes is high (Table 2). These incidence rate estimates are based on two follow-up studies of randomised trials, both of which were from developed countries where the event rates are likely to be lower than those observed in the countries participating in CORONIS. These studies, therefore, are likely to represent a conservative estimate of the anticipated event rates. One study was following a trial of closure versus non-closure of the peritoneum [12] and the other following single versus double layer closure of the uterine incision^13^. Both studies were small (n = 145 and 144 women) and the estimates of some of the outcomes are therefore imprecise. For example, the estimate of uterine dehiscence is based on 1 event out of 145 women, giving an incidence of 0.69% with a 95% confidence interval of 0.12% to 3.8%. The estimate of dyspareunia is based on 27 events out of 144 women giving an incidence of 19% with a 95% confidence interval of 13% to 26%.

**Table 2 T2:** power to detect a specified difference for a fixed sample size

**Outcome examples**	**Event rate in 1st group e.g. single layer closure**	**Event rate in 2nd group e.g. double layer closure**	**Absolute risk difference**	**Power available to detect this difference**

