A systematic review of the literature has shown that to date there have been only three long-term follow-up studies of the existing randomised trials of caesarean section techniques. One investigated the long-term effects of single versus double layer uterine closure and two studies assessed long- term outcomes of trials comparing closure versus non-closure of the peritoneum in a subsequent pregnancy [10,13,14]. The sample sizes of these follow-up studies are small and included only 18% of the women randomised into the original trials for two of them [10,13] and 51% for the third [14]. In the only study that compared single versus double layer uterine closure, no statistically significant difference was found on the following outcomes: inter-pregnancy interval, vaginal delivery, length of hospital stay, preterm delivery, amnionitis, postpartum endometritis, placental abruption, postpartum haemorrhage, blood transfusion or uterine dehiscence. However, this was only based on a sample size of 145 women out of the 906 randomised in the original trial [13]. From the two follow-up studies of randomised trials comparing closure versus non-closure of the peritoneum (209 women in total), no differences were observed in terms of intra-abdominal adhesions (65 women evaluated out of the 360 originally randomised) [10], abdominal pain, dyspareunia, constipation, urinary symptoms and infertility (144 women included out of the 280 originally randomised) [14].

Given the relatively low incidence of uterine rupture (0.4 to 0.6% for women undergoing a trial of labour versus 0.2% for those having elective repeat caesarean) and dehiscence (1.1%) [17], attempts to detect differences in these outcomes between different surgical techniques with adequate power is challenging. However, the one large observational study that has looked at this outcome is weakened by several potentially interrelated factors [15]. For example, the caesarean technique used changed from mainly double layer closure to mainly single layer closure during the period studied, and the selection criteria for trial of labour may have changed in this time too. Thus women who had single layer closure may have been more likely to have a trial of labour. Well conducted follow-up studies of randomised trials remain the best option to evaluate these outcomes reliably.

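### The 4% vs 5.9% behind the stated 92% power for uterine rupture or dehiscence has no stated source and is well above every rate the protocol quotes, so it cannot be called conservative

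*Protocol article*

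**What the plan says.** Under Sample size and power, the protocol article describes power as high for the outcomes in Table 2 and explains where the rates come from: "These incidence rate estimates are based on two follow-up studies of randomised trials". Both studies were done in developed countries, where the authors expect rates to be lower than in the CORONIS countries. They conclude: "These studies, therefore, are likely to represent a conservative estimate of the anticipated event rates".

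The same paragraph says the two studies were small and some estimates imprecise. Its example is that "the estimate of uterine dehiscence is based on 1 event out of 145 women, giving an incidence of 0.69"%; the 95% limits printed for this estimate are 0.12% and 3.8%.

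The Table 2 row reads "Uterine rupture or dehiscence 4% 5.9% 1.9% 92"%. It stands in the block headed "For women who have a subsequent pregnancy (number estimated to be ~5,900"). The table note says the calculations "assume equal numbers in each comparison and a 2-5% level of statistical significance".

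The background (Summary of existing evidence) quotes other figures: "Given the relatively low incidence of uterine rupture (0.4 to 0.6% for women undergoing a trial of labour"), 0.2% for elective repeat caesarean, and 1.1% for dehiscence. It calls adequate power for these outcomes challenging.

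**The concern.** Readers are told that the Table 2 rates rest on the two studies and, if anything, understate what will be seen. For this row the only source figure shown is 0.69%, for dehiscence. The row starts at 4%, which is 4 / 0.69 = 5.8 times as high and slightly above the upper confidence limit quoted for that component. The dyspareunia row, by contrast, follows its source: 27/144 = 18.75%, entered as 19%. The background's view that power is challenging and the later statement that it is high also point in different directions for the same outcome.

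The row matters. In Table 1, rupture and dehiscence are each main comparisons for two of the five pairs (single vs double layer closure, and catgut vs Polyglactin-910), and the background names scar integrity in later pregnancies among the most important long-term questions. If the event rate turns out nearer to the quoted figures, a null result set against a stated 92% could be taken as stronger reassurance than the data can give.

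**Working it through.** **Inputs**
- Number analysed: about 5,900 per pair with equal arms, so n = 2,950 per arm (Table 2 and its note).
- Significance level: the note's 2-5% is read as two-sided 5%, which reproduces the table. A two-sided 2% level would give 85% for this row.
- Row rates: 4% vs 5.9%, so RR = 5.9 / 4 = 1.475 and the difference is 1.9 points.
- Quoted rates: dehiscence 0.69% (Sample size and power); dehiscence 1.1% and rupture 0.2% to 0.6% (background). The highest sum of the background rates is 1.1% + 0.6% = 1.7%. The protocol does not state this sum; it is an upper bound from the quoted components.

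**Formula** (normal approximation, pooled variance under the null)

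power = Φ{ [ d√n − 1.96 √(2p̄(1−p̄)) ] / √(p₁(1−p₁) + p₂(1−p₂)) }, with d = |p₂ − p₁| and p̄ the mean of p₁ and p₂.

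**The plan's own figure.** With 4% vs 5.9%: d√n = 0.019 × √2950 = 1.032; 1.96 × √(2 × 0.0495 × 0.9505) = 0.601; denominator 0.3065. Then (1.032 − 0.601) / 0.3065 = 1.41 and Φ(1.41) = 92.0%. The stated 92% reproduces.

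**The source interval.** 1/145 = 0.69%, with Wilson 95% limits of 0.12% and 3.80%, as printed.

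**Quoted rates, relative risk held at 1.475**

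| Lower rate | Higher rate | Expected events per arm | Power |
|---|---|---|---|
| 0.69% | 1.02% | 20 vs 30 | 27.7% |
| 1.1% | 1.62% | 32 vs 48 | 41.0% |
| 1.7% | 2.51% | 50 vs 74 | 58.0% |
| 3.8% | 5.61% | 112 vs 165 | 90.6% |
| 4% | 5.9% | 118 vs 174 | 92.0% |

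**Quoted rates, absolute difference held at 1.9 points**

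| Lower rate | Higher rate | Implied RR | Power |
|---|---|---|---|
| 0.69% | 2.59% | 3.8 | over 99% |
| 1.1% | 3.0% | 2.7 | over 99% |
| 1.7% | 3.6% | 2.1 | over 99% |

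**Smallest RR detectable with 80% power, 2,950 per arm:** 2.1 at 0.69% (vs 1.44%), 1.8 at 1.1% (vs 2.00%) and 1.6 at 1.7% (vs 2.78%).

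**The case against.** Several points on the other side have weight.

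- **There is no miscalculation.** This stands. A reader might infer from the contrast between 92% and 28% to 58% that the power was computed wrongly. It was not; the dispute is over the inputs and their description.
- **The 28% to 58% range depends on holding the relative risk.** This stands as a condition. Table 2 has a column for the absolute difference, and holding 1.9 points keeps power above 99%. That does not rescue the row, because it requires the risk to rise 2.1- to 3.8-fold, while the protocol speaks of modest differences. The relative risk is also the protocol's comparison measure for dichotomous outcomes (Primary comparative analyses).
- **0.69% and its 3.8% limit are for dehiscence alone, while the row is rupture or dehiscence.** This stands. The factor of 5.8 and the comparison with 3.8% set a composite against one component. The 1.7% sum allows for rupture and is still less than half of 4%, though it rests on a different citation from the two studies named.
- **Rates in the seven countries may be higher.** The protocol says so, and 1/145 hardly constrains the rate. A reader might infer that 28% to 58% is the true power. The documents do not support that: the true rate is unknown, and 3.8% would give about 91%. But an allowance for higher local rates, if one was made, is not stated. The text presents the rates as conservative before any such allowance.
- **The row is illustrative and the imprecision is disclosed.** The follow-up size is fixed and was not derived from this row, and the section prints the 1/145 count with its interval. This lowers the stakes for the design. It does not supply a source for 4%, and this row is the only power statement for the outcome.

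**Conclusion.** The point holds as an inconsistency between the stated basis of the rates and the rates used. For uterine rupture or dehiscence, 4% vs 5.9% has no stated source, is well above the quoted 0.69% and the at most 1.7% combined, and is not conservative relative to either. The 92% is right for its inputs, but the basis claimed for those inputs does not support it.

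At the quoted rates power is about 28% (0.69%), 41% (1.1%) and 58% (1.7%). This assumes a relative risk of 1.475, 2,950 women per arm, a two-sided 5% test, and no uplift for the participating countries. It shows how far the answer depends on the base rate and does not estimate the power the study will have. The cohort, the outcomes and the analysis are unaffected.

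**What to change.** - In Table 2, show for this outcome the power, or the smallest relative risk detectable with 80% power, at base rates of about 0.7%, 1.1% and 1.7%, and state that the relative risk is held. On the figures above this is 28%, 41% and 58%, or relative risks of 2.1, 1.8 and 1.6.
- Keep the 4% vs 5.9% row only if its source is given, or if the uplift assumed for the participating countries is stated and justified.
- Delete or qualify the statement that the rates are conservative, and limit the claim of high power so that it does not cover this outcome without a condition on the base rate. That also brings the section into line with the background.

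The cost is one table row (or three) and a sentence or two. The stated power becomes less favourable; nothing in the design, sample or analysis changes.

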**For all women (number estimated to be ~7,400)**				
Involuntary infertility	3%	4.5%	1.5%	92%
Subsequent pregnancy	48%	44%	4%	93%
Dyspareunia	19%	16%	3%	92%
